## Methods

We will perform a multi-center international cross-sectional interview study at six centers in four countries: two in Hamilton, Ontario, Canada; one in Buffalo, USA; one in Oslo, Norway; and two in Helsinki, Finland.

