#### Primary and secondary outcome(s)

We will calculate the mean threshold reduction in VTE at which women were willing to accept use of LMWH and the 95% confidence interval around the mean. We will calculate the proportion of women who are willing to take prophylactic LMWH and the associated 95% confidence intervals The mean and standard deviation of the visual analog scale ratings for each health state will also be determined.

Multiple variable linear regression will be undertaken to explore determinants of the VTE threshold, as determined in the probability trade-off exercise. In this analysis, VTE threshold will be the dependent variable and the independent variables will be the previous experience of VTE (categorized as severe, moderate, or mild), previous experience with prophylactic LMWH (yes, problematic; yes, no problems; no prior experience), level of education (some postsecondary versus no postsecondary) and study site.

We will perform a standard multiple variable logistic regression to explore the determinants on the choice for or against LMWH prophylaxis in the real life scenario. The dependent variable will be the choice for or against LMWH prophylaxis and the independent variables will be the previous experience of VTE, previous experience with LMWH prophylaxis, level of education, study site, and high or low risk for recurrence.

A hierarchical logistic regression in which the dependent variable will be the choice to receive or not receive LMWH from the results of the hypothetical scenario exercise will also be undertaken. The independent variable within the first level will be the magnitude of the absolute risk reduction (high, moderate and low). The second level, nested within the absolute risk reduction will include previous experience of VTE, previous experience with LMWH, level of education and study site. Finally, we will perform a multiple variable linear regression with the threshold as the dependent variable and with utilities as independent variables. We will evaluate the interaction term of utilities and VTE in the regression model.

Using an independent sample *t*-test, we will evaluate if the responses between women who are pregnant or planning a pregnancy are different to those who are not.

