The scatter plots of each of the participants’ utilities, as determined by the FT ratings of the health states, and the VTE thresholds will be examined to evaluate the relation between participant utilities and their VTE threshold. We will calculate Pearson’s correlations between each of the utilities for the health states and the threshold.

We believe that a lack of consistency in patient responses is the best way to detect a problem with individual patient understanding, which if it occurs frequently enough (i.e. > or = 25% of participants), may represent a problem in the way in which the information is being presented. Therefore, we will review consistency data after 10, 20, 30, and 40 women have been enrolled. We will also examine consistency data prior to these pre-specified points if there is concern about the level of inconsistency in patient responses. Table 4 contains frequencies of inconsistent responses, which would favor a review of the study scripts and presentation tools. We will also compare responses between women who are consistent and those who are inconsistent in their responses, even after they are provided with the opportunity to correct discrepancies in their responses. If the results differ between these groups, our primary analysis will include only those with consistent responses.

**Table 4 T4:** Guidelines for frequencies of inconsistent responses favoring review of study scripts and presentation tools

**Frequency of inconsistent response**	**%**	**Lower bound of 95% CI**
> or = 5/10	50.0	23.7
> or = 8/20	40.0	21.9
> or = 10/30	33.3	19.2
> or = 12/40	30.0	18.1

For all key analyses above, we will compare results and the pattern of responses in women who answer the “understanding” questions correctly and those who do not. A similar comparison will also be made according to the interviewer’s impression of patient understanding. If the results differ between women categorized as understanding and not understanding, our primary analysis will focus on women with an apparent high level of understanding.

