## Discussion

Producing guidelines for management of pregnant women with prior VTE is problematic because there is little reliable information in the literature to guide the value and preference judgments necessary for making recommendations. Clinical management is challenging because of the lack of a standardized approach to presenting information and eliciting patients' choice. Our study will be the first to explore the preferences of women at risk of pregnancy-related VTE with respect to the use of antithrombotic therapy.

Our study has several strengths. We will address some of the limitations of the previous studies in the field of decision-making. These studies using direct choice methods, and in particular the probability trade-off, have shown many extreme choices that raise doubts about whether all patients understood the decisions they were making [84,88]. We pilot-tested standardized scripts that were reviewed by expert and non-expert clinicians, and allied health professionals to ensure appropriate readability and understandability. We are presenting probability information in three different ways. We have trained research assistants and will undertake quality control of the data as it accumulates.

We will check for consistency in the participants’ choice to either take or not take LMWH for a given probability of DVT. Participants will have discrepancies brought to their attention and will have the opportunity to change their responses. We will use standardized questions to test understanding of the information presented and the interviewer will provide a rating of the extent to which she or he believes the respondent had a clear understanding of the questions and their confidence in this assessment. Our analysis will include an exploration of whether patterns of responses differ (1) between those with an apparently high level of understanding and those who do not, (2) between those whose answers are consistent and those with inconsistent answers, and (3) between those who, according to the interviewer’s impression of patient understanding, show a correct understanding and those who do not. Finally, our multicenter international design limits the influence of local views about the use of LMWH prophylaxis for prevention of recurrent pregnancy-associated VTE and enhances generalizability.

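### The exploratory regression of VTE threshold on thermometer utilities leaves out study site, although the plan's other three regressions include it

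*Protocol article*

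**What the plan says.** All of this is in the Protocol article. The Methods section describes a "multi-center international cross-sectional interview study at six centers in four countries".

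Under Primary and secondary outcome(s), four regressions are specified:

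- Linear model for determinants of the VTE threshold. The covariate list ends "level of education (some postsecondary versus no postsecondary) and study site".
- Logistic model for the real-life choice. The list includes "previous experience with LMWH prophylaxis, level of education, study site, and high or low risk for recurrence".
- Hierarchical logistic model for the hypothetical scenarios. The second level includes "previous experience with LMWH, level of education and study site".
- Linear model of threshold on utilities: "we will perform a multiple variable linear regression with the threshold as the dependent variable and with utilities as independent variables". The only further term is given by "We will evaluate the interaction term of utilities and VTE in the regression model".

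The same section adds scatter plots and Pearson "correlations between each of the utilities for the health states and the threshold". No adjustment or stratification by site is stated for these. The Discussion says that the multicenter international design "limits the influence of local views about the use of LMWH prophylaxis".

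**The concern.** Two models in the plan have the same dependent variable, the VTE threshold. One treats study site as a possible determinant of it and the other does not. If centers differ in average threshold and also in average thermometer rating, those differences enter the pooled slope of threshold on utility. The result then blends the relation among women at the same center with an association among a handful of center averages.

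Averaging over many centers does make a mean less dependent on local practice, as the Discussion says. It gives no such protection to an association between two measured variables, because differences between center means contribute directly to the covariance. At stake is the reading of this one exploratory analysis. A relation between valuations and thresholds could appear where none exists within centers, or a real one could be weakened.

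**Working it through.** **No figure to reproduce.** The document gives no expected correlation, power or between-center variance for this analysis. The check is therefore a comparison of covariate lists, followed by a range of assumed values.

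**Covariate lists.** Site appears in three of the three other regressions and not in the utility regression.

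**How center differences enter.** Let r_w be the within-center correlation and r_b the correlation of center means. Let s_x and s_y be the shares of utility and threshold variance that lie between centers. Then

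pooled r = r_w × √((1 − s_x)(1 − s_y)) + r_b × √(s_x × s_y),

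which for s_x = s_y = s becomes r_w(1 − s) + r_b × s.

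**Worked example (all values assumed).** Within-center r = -0.30 with SDs 15 (rating) and 5 (threshold); center means with SDs 8 and 2.

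- Shares between centers: 64/289 = 22% of rating variance and 4/29 = 14% of threshold variance.
- Within covariance: -0.30 × 15 × 5 = -22.5.
- Total SDs: √(225 + 64) = 17.0 and √(25 + 4) = 5.39; product 91.6.
- r_b = +0.8: between covariance 0.8 × 8 × 2 = 12.8; pooled r = -9.7/91.6 = -0.11.
- r_b = +0.5: between covariance 8.0; pooled r = -14.5/91.6 = -0.16.
- r_b = 0: pooled r = -22.5/91.6 = -0.25.
- r_b = -0.8: pooled r = -35.3/91.6 = -0.39.

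With 100 women, |r| must exceed about 0.20 for two-sided significance at 0.05. The first two cases would miss it and the last two would not.

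**Simulation over a range of s (assumed).** 100 women, six sites of 16 or 17 in four countries, differences between countries only, one utility, 4,000 runs per setting, two-sided 0.05. Least squares was fitted without and with site indicators. The columns for r_w = 0 show false-positive rates and those for r_w = -0.30 show power. Country means are perfectly correlated (r_b = +1), which is the worst case.

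| s | Formula r, r_w = 0 | No site | With site | Formula r, r_w = -0.30 | No site | With site |
|---|---|---|---|---|---|---|
| 0 | 0 | 0.06 | 0.06 | -0.30 | 0.87 | 0.85 |
| 0.05 | 0.05 | 0.07 | 0.04 | -0.235 | 0.72 | 0.85 |
| 0.10 | 0.10 | 0.14 | 0.05 | -0.17 | 0.55 | 0.85 |
| 0.20 | 0.20 | 0.34 | 0.06 | -0.04 | 0.37 | 0.85 |
| 0.30 | 0.30 | 0.55 | 0.05 | +0.09 | 0.33 | 0.85 |

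The average simulated pooled r is less extreme than the formula. For r_w = -0.30 it is -0.25, -0.21, -0.12 and -0.02 at s = 0.05 to 0.30, because only four countries are drawn. Power counts significant results of either sign, so at s = 0.30 some of them point the wrong way.

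When country means are drawn independently (r_b = 0), the false-positive rate without site is 0.05, 0.07, 0.13 and 0.22 at s = 0.05, 0.10, 0.20 and 0.30. Power without site is 0.83, 0.79, 0.71 and 0.63. So few means can line up by chance.

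**The case against.** The case for leaving the plan alone has several parts.

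- **The analysis is secondary and exploratory.** This stands. The mean threshold and its confidence interval, the willingness proportions and the utility means do not depend on it.
- **Agreement between direct choice and utility-based decisions is tested elsewhere.** This stands. A reader might infer that this regression is the plan's test of whether the two approaches agree, or that a distorted correlation would label individual women incoherent. The document does not support that. The personalized decision analysis compares model results with the chosen threshold for each woman, and individual coherence is handled by the consistency and understanding checks.
- **Pearson correlations are unadjusted by nature.** This stands. Read beside scatter plots, they are legitimate description.
- **The stated aim is the relation across participants.** This stands in part. A reader might infer that only the within-center relation is of interest, but the document does not say so. If women in one country value the burden of injections differently and set different thresholds for that reason, this belongs to the relation. Pooled and adjusted results therefore answer different questions, which is a reason to show both.
- **Standardized scripts are used across centers and interviewers.** They should reduce interviewer differences. They cannot guarantee that women in four countries use a rating scale alike. The Discussion acknowledges local views but predicts no difference between sites in ratings or thresholds.
- **The utility model is only sketched, and the full analysis plan may add site.** This is possible. Yet the neighboring sentences name site for every other model, including one with the same outcome, so the omission is not explained by the brevity of an article.
- **The large distortions need large, aligned center differences.** This stands, and it limits the size of the claim.

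**Conclusion.** The point holds as an inconsistency in one exploratory regression. The plan adjusts for site in three models, including the other threshold model, and not in the model relating threshold to utilities.

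The possible distortion runs from small to material. At a between-center share of about 5% or less it is small: the false-positive rate is at most 0.07, and the largest power loss, under perfectly opposed means, is from about 0.85 to 0.72. At 10 to 20% or more it is material when center means are strongly aligned or opposed, with false-positive rates of 0.14 to 0.34 and power of 0.55 to 0.37. These figures rest on assumed variance shares, an assumed within-center correlation of -0.30, one utility and near-equal site sizes, none of which the document gives.

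It would go too far to conclude that the relation will be distorted, that the pooled correlations are an error, or that the primary result is in doubt. The primary mean threshold and the woman-by-woman decision-analysis comparison are not affected.

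**What to change.** Add study site to the regression of threshold on utilities, or country if some sites recruit few women. Keep the pooled Pearson correlations as description and report partial correlations given site beside them. Marking scatter-plot points by center would let readers see any center pattern.

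The cost is one sentence in the plan and no new data. Six sites use 6 − 1 = 5 degrees of freedom among 100 women; four countries use 3. If centers do not differ at all, power in the simulation falls only from 0.87 to 0.85.

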### Outcomes

The primary outcome measure will be the minimum threshold reduction in VTE risk in the probability trade-off exercise at which women switch from declining to accepting LMWH prophylaxis (which we will refer to as the “VTE threshold”).

Secondary outcomes will include:

(i) women’s willingness to take prophylactic LMWH according to their classification as either high or low risk for recurrence,

(ii) women’s willingness to take prophylactic LMWH for each of the three hypothetical scenarios

(iii) Utilities for each of the five health states assessed in the FT (the burden of prophylactic LMWH use during pregnancy – either the standardized experience or the patient’s prior experience-, a pregnancy with the participant’s own most recent VTE, a standardized description of pregnancy-related DVT, a standardized description of pregnancy-related PE, and a standardized description of an obstetrical bleed [Additional file 1: Appendix I]).

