#### Sample size

Previous research from our group in patients with atrial fibrillation [83], and from other groups studying non-pregnant women with prior VTE [85], suggests that moderately precise estimates of patient preference can be obtained with sample sizes of approximately 100 participants. In the most relevant recent experience, co-investigators on the current project enrolled 96 patients with risk factors of atrial fibrillation [85]. The primary endpoint of that study was the threshold number of bleeds patients were willing to accept over 2 years given a reduction of 3 strokes over a 2-year period. This is directly analogous to the primary endpoint of our study, the VTE threshold. In the atrial fibrillation study, the mean number of bleeds that patients were willing to accept was 15. With a sample size of 96 patients, the confidence interval around the mean number of acceptable bleeds was 12 to 18, which we judged to be an acceptable range of uncertainty. The range of bleeds that patients chose varied over an extremely wide range (from 0 to 100). The entire range of possible VTE prevented for LWMH to be acceptable in the current study will range from 0 to 16, a much narrower range, which is certain to result in much smaller variability, and thus an appreciably smaller confidence interval. We are, thus, confident that our projected sample size of 100 will yield a sufficiently precise estimate of our primary outcome, the mean number of VTE prevented required to tolerate LMWH.

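### The population for the primary mean threshold depends on an undefined comparison of the results, so no single primary estimand is fixed and 95% coverage is not guaranteed

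*Protocol article*

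**What the plan says.** All references are to the protocol article.

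- **Outcomes** makes the threshold primary: "The primary outcome measure will be the minimum threshold reduction in VTE risk in the probability trade-off exercise". **Primary and secondary outcome(s)** summarises it by the mean "and the 95% confidence interval around the mean".
- The same analysis section compares women who remain inconsistent after a chance to correct their answers with women who are consistent, and adds: "If the results differ between these groups, our primary analysis will include only those with consistent responses".
- It then turns to understanding: "For all key analyses above, we will compare results and the pattern of responses in women who answer" the understanding questions correctly with those who do not. The key analyses include the primary one. A further grouping follows: "A similar comparison will also be made according to" the interviewer's impression. If results differ, "our primary analysis will focus on women with an apparent high level of understanding".
- **Sample size** argues precision for the full number only: "our projected sample size of 100 will yield a sufficiently precise estimate of our primary outcome".

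No other section fixes the primary population. The Discussion lists the same three comparisons, but only as an exploration. The comparison by pregnancy status is handled differently: it is tested and reported, and the primary set stays as it is.

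**The concern.** Women are removed from the primary analysis only when their answers differ from the others', that is, when removing them moves the estimate. The article states no test, margin or outcome by which to decide that results differ. It does not say how the two rules combine, or which measure of understanding governs if the questions and the interviewer disagree. The mean might describe all women, consistent women, women who understood, or an overlap of these, and which one is unknown until the data are seen. An ordinary 95% interval computed on the chosen set takes no account of the choice.

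Consistency is judged across exercises about accepting or declining LMWH, so the screen may itself be related to the threshold. The result is intended for guideline developers, who need to know whose mean it is.

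**Working it through.** **The plan's own figure.** The sample size of 100 cannot be re-derived, because no SD or target width is given for the threshold. The cited atrial fibrillation study (n = 96, mean 15, interval 12 to 18) implies SD = 3 × √96 / 1.96 = 15.0 on its own scale. The article says only that the VTE threshold "will range from 0 to 16, a much narrower range", so an SD has to be assumed here.

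**Inputs from the article:** n = 100; a mean with a 95% interval; restriction to consistent women if results differ. The article also gives 25% inconsistent, but as the level that may signal a presentation problem, not as a forecast.

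**Assumptions:** normally distributed thresholds; SD 5 per 100 (SD 4 as a check); *differ* read as two-sided p < 0.05 in a t-test; 25% or 10% inconsistent; true group difference 2, 3 or 4 per 100.

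**Why both targets suffer.** With share f inconsistent and difference d, the two candidate means lie f × d apart. At f = 0.25 that is 0.25 × 2 = 0.50, 0.25 × 3 = 0.75 and 0.25 × 4 = 1.00 per 100. The interval half-width for all women at SD 5 is 1.96 × 5 / √100 = 0.98. The rule reports one mean in some studies and the other in the rest.

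**Simulation of the consistency rule alone (SD 5, 25% inconsistent):**

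| True difference per 100 | Studies that switch set | Coverage, all-women mean | Coverage, consistent-women mean |
|---|---|---|---|
| 2 | 40% | 88% | 88% |
| 3 | 73% | 75% | 88% |
| 4 | 92% | 60% | 92% |

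- **10% inconsistent, same differences:** about 89–93% for the all-women mean and about 93% for the consistent-women mean.
- **SD 4, 25% inconsistent, difference 2:** the set switches in 57% of studies; coverage is 82% (all women) and 88% (consistent women).
- **Population fixed in advance:** about 95% for that population's own mean.
- **No true difference, one screen, SD 4:** 93.8–94.4%, a loss of about 1 point.
- **Target allowed to move with the selected set:** 93.5–95.8%. Coverage is then near nominal, but the quantity being estimated changes from study to study.

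**Precision after restriction.** If 25 women are excluded, the interval widens by √(100/75) = 1.155. At SD 5 the half-width goes from 0.98 to 1.96 × 5 / √75 = 1.13 per 100.

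**The case against.** The case for the plan has several parts.

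- **The target may be valid preferences.** The article treats persistent inconsistency as the best sign of poor understanding, so the consistent women may be the real target. This stands. On that view the loss is about 3 to 7 points (88–92% with 25% inconsistent), and always analysing all women would do worse for that target: 84%, 71% and 54% at differences of 2, 3 and 4. It argues for choosing the target in advance. It does not rescue a rule that falls short for both targets.
- **25% inconsistent is pessimistic.** This also stands. Women may correct their answers, and consistency is reviewed after 10, 20, 30 and 40 women, which can prompt revision of the scripts. The 10% figures must be shown beside the 25% ones.
- **The contingency is declared in advance, and details can go to an analysis plan.** This stands in part. The direction of the restriction is declared, but its trigger is an undefined look at results that include the primary outcome. That is a rule stated badly, not a detail left out.
- **The study is descriptive, with no test on the primary mean.** True, but the mean and its interval are the primary result.

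A reader might infer more than the text supports. Three screens could suggest eight possible primary sets (2³), and 1 − 0.95³ = 14.3% chance switching with no true difference. Both are upper-end readings. The article has two rules, the second speaks of a focus and not clearly of exclusion, and the 14.3% needs three independent 5% screens although all three probe related things.

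**Conclusion.** The concern holds in this form: the primary population is conditional on the results, the condition is undefined, and the study therefore has no single fixed primary estimand. Nominal 95% coverage is not guaranteed for the all-women mean or the consistent-women mean.

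The size depends on assumptions that the article does not supply: the SD, the share inconsistent, the group difference and the reading of *differ*. The loss is material when the groups differ moderately and many women are inconsistent, and modest when few are.

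Two stronger conclusions are tempting and unsupported. One is that the interval is simply invalid: with no true difference the loss from one screen is about 1 point, and coverage of whichever mean is selected stays near nominal. The other is that coverage falls to 60%: that figure needs all women as the target, 25% inconsistent and a difference of 4 per 100. The loss of precision from a smaller set is a minor point.

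**What to change.** Delete the two conditions that tie the primary population to whether results differ. Name one primary population unconditionally, before results are seen. Either choice is workable:

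1. All women who complete the probability trade-off.
2. A restricted set defined in advance by consistency, by the standardized understanding questions, or by both. This is closer to the article's own rationale. Precision should then be restated for the reduced number (an interval about 1.15 times as wide if 25 women are excluded).

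Report the other populations, including the one based on the interviewer's impression, as sensitivity analyses whatever they show.

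The cost is a change of wording, with no new data collection. The downside is small and depends on the choice: the first keeps some noisy responses in the primary mean, and the second gives a slightly wider interval.
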